## Method

### Study design

Details about this trial are captured in the SPIRIT (Standard Protocol Items: Recommendations for Interventional Trials) checklist [54, 55] in Appendix A of the online supplemental materials (OSM) and Fig. 1. This study is a two-arm, parallel-group RCT that aims to test the efficacy of Digital PAI relative to a Self-Monitoring Placebo control in adults with mild-to-moderately severe anxiety or depression. After providing informed consent and completing the Qualtrics-administered baseline self-report battery, participants will be randomized in a 1:1 ratio (*n* = 600 per condition) using a computer-generated random number sequence embedded in the Qualtrics platform. In other words, participants are randomized into the Digital PAI or Self-Monitoring Placebo control group at the end of the baseline assessment using the built-in randomizer function in Qualtrics. The sequence is stratified by race and sex to ensure balanced allocation across key demographic strata. Immediately after completing the baseline assessment, Qualtrics automatically assigns participants to either the 6-week, low-intensity, guidance-on-demand Digital PAI or the 6-week Self-Monitoring Placebo, both of which are accessed via the mEMA Ilumivu software. The allocation sequence is concealed from the lead principal investigator (PI) and study analyst via automated assignment coding; both remain blinded to treatment group assignments until after data collection is complete.

**Fig. 1 Fig1:**
[figure not shown]
Standard Protocol Items: Recommendations for Interventional Trials (SPIRIT) Schedule Note. ACS, Attentional Control Scale; ASRM, Altman Self-Rated Mania; ATQ, Automatic Thoughts Questionnaire; BLERT, Bell Lysaker Emotion Recognition Test; Brief COPE, Brief Coping Orientation to Problems Experienced; CDS, Cognitive Distortions Scale; CRQ, Cultural Relevance Questionnaire; CTQ, Childhood Trauma Questionnaire; DARS, Dimensional Anhedonia Rating Scale; EMA, ecological momentary assessment; EMI, ecological momentary intervention; ERQ, Emotion Regulation Questionnaire; GAD-7, Generalized Anxiety Disorder-7; GADQ-IV, Generalized Anxiety Disorder Questionnaire-Fourth Edition; GNG, Go/No-Go; HAT, Helpful and Hindering Aspects of Therapy; IRI, Interpersonal Reactivity Index; MHC-SF, Mental Health Continuum Short Form; NEO-PI-R, Neuroticism, Extraversion, Openness Personality Inventory-Revised; PANAS, Positive and Negative Affect Schedule; PDSR, Panic Disorder Self-Report; PHI, Pemberton Happiness Index; PHQ-9, Patient Health Questionnaire-9; PSAS, Pre-Sleep Arousal Scale; PSQI, Pittsburgh Sleep Quality Index; PSS, Perceived Stress Scale; PVSS, Positive Valence Systems Scale; RSES, Rosenberg Self-Esteem Scale; SCS-SF, Self-Compassion Scale-Short Form; SCI, Sleep Condition Indicator; SHPS, Sleep Hygiene Practice Scale; SPIRIT, Standard Protocol Items: Recommendations for Interventional Trials; STQ, Satisfaction with Treatment Questionnaire; UCLA, University of California in Los Angeles; WCST, Wisconsin Card Sorting Test

This RCT employs a single-assessor-blinded design. Specifically, outcome assessors involved in baseline and follow-up assessment protocols, as well as the statistician responsible for the primary efficacy analyses, stay blinded to participant allocation. All treatment groups are labeled with non-identifiable codes, and treatment group assignment data are concealed from these research personnel until after the data collection is complete. Unblinding procedures will not be conducted, as they are not required to ensure participant safety in this RCT. Relatedly, no formal patient or public involvement (PPI) was incorporated in the study design, conduct, or reporting of this trial. However, participants will be invited to offer qualitative feedback on their user experiences, which will inform and improve future iterations of the intervention. Additionally, participants may continue with treatment-as-usual, including medication or psychotherapy, throughout this trial. Concurrent treatment will be captured at baseline assessment and considered in exploratory analyses.

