### Statistical analysis plan

#### Data processing and missing data management

All preprocessing steps and data analyses will be conducted using the *R* software [113]. Using an intention-to-treat (ITT) approach, we will estimate between-group treatment efficacy for continuous and binary clinical outcomes [114]. A complier average causal effects (CACE) analysis will also be conducted to determine treatment efficacy between high- and low-potential engagers [115]. Before conducting the key data analyses, a series of preprocessing steps will be undertaken. These include anomaly diagnostics, assumption checks (e.g., linearity, multivariate normality), and random forest imputation of missing data. Random forest imputation with the *missRanger* package [116] will be used instead of multiple imputation because it better handles nonlinear associations and interactions and generates improved performance even under missing not-at-random (MNAR) conditions [117]. Sensitivity analyses will be conducted by examining outcomes under two alternative missing data management approaches, full information maximum likelihood (FIML) and multiple imputation [118]. The point estimates and 95% confidence intervals (CIs) of all effect sizes, Cohen’s *d* for continuous outcomes [119], as well as odds ratios [ORs] and risk ratios [RRs] for binary outcomes [120], will also be computed consistently.

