#### Statistical approaches for primary and secondary outcomes

Prospective analyses of primary and secondary continuous outcomes, such as anxiety and depressive symptom severity (GAD-7 and PHQ-9), anhedonia (DARS), and PA (PANAS), will be analyzed using multilevel modeling (MLM) with restricted maximum likelihood estimation (REML). Piecewise MLM will be used to assess between-group differences in changes across unique timeframes (e.g., baseline to post-treatment vs. post-treatment to 3-month follow-up), enabling the estimation of distinct linear slopes before and after critical time points to model nuanced changes in clinical outcomes over time. The MLM models will consist of fixed effects of group (Digital PAI vs. Self-Monitoring Placebo) and two-way group-by-time interaction to account for within-person associations. We will use the *nlme* package [121] for all analyses, assuming random intercepts and slopes for all models. Level 1 will model within-person changes over time, and Level 2 will capture between-person factors. All outcomes will be modeled across recurring time points (baseline, mid-treatment [Week 3], post-treatment [Week 6], as well as 3-month, 6-month, and 12-month follow-ups), aligned with this RCT’s assessment schedule. Covariates will include demographic variables (e.g., age, sex), baseline symptom severity, and device wear time, where relevant, for variables that significantly differed between groups at baseline. Between- and within-group effect sizes will be computed for all outcomes of interest [119, 122]. For binary clinical outcomes, such as depression remission indexed by PHQ-9 ≤ 4, generalized estimating equations (GEE) will be utilized to estimate between-group efficacy across all time points and follow-ups, accounting for repeated assessments with an exchangeable working correlation structure [123, 124]. Standard MLM with a logistic linking function will also be conducted as a sensitivity analysis for binary outcomes [125].

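### The statistician's blind is guaranteed only to the end of data collection, not through the primary analysis it is meant to protect

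*Protocol article*

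**What the plan says.** The blind is described in two places in the protocol article, both under Method, Study design.

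- **First paragraph.** Allocation is concealed from the lead principal investigator and the study analyst, and "both remain blinded to treatment group assignments until after data collection is complete".
- **Paragraph after Fig. 1.** Outcome assessors, together with "the statistician responsible for the primary efficacy analyses, stay blinded to participant allocation". The means is coding: "All treatment groups are labeled with non-identifiable codes". The duration follows: "treatment group assignment data are concealed from these research personnel until after the data collection is complete". The paragraph then adds: "Unblinding procedures will not be conducted, as they are not required to ensure participant safety in this RCT".

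The analysis sections describe what happens once the data are in.

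- **Data processing and missing data management.** "Before conducting the key data analyses, a series of preprocessing steps will be undertaken". "These include anomaly diagnostics", assumption checks and random forest imputation. The section does not say whether this work is done blind.
- **Statistical approaches for primary and secondary outcomes.** Continuous outcomes, including GAD-7 and PHQ-9, are modelled over baseline, Week 3, Week 6 and Months 3, 6 and 12. Covariates are to be included, where relevant, "for variables that significantly differed between groups at baseline".

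Under Treatment-specific assessments, three measures (CRQ, HAT and STQ) are given to the Digital PAI arm alone.

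**The concern.** Blinding a statistician guards against decisions that tilt the result towards a favoured arm. Such decisions arise mainly after the data are in, when unusual values are dealt with, covariates are chosen and models are checked. A blind promised only up to the end of data collection may stop just before the work it exists for.

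This matters more here because both primary outcomes are self-reported, and the control participants complete mood monitoring without therapy content. Blinding on the analysis side is thus one of the main remaining safeguards. If it lapses early, a reader of the results cannot tell from the protocol whether judgement calls in the GAD-7 and PHQ-9 analyses were made with the arms known.

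**Working it through.** No arithmetic applies. The check sets the statements on blinding beside those on analysis and asks whether the guaranteed blind and the primary analysis overlap.

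1. **When does the promised blind end?** Both statements under Study design name the same event, completion of data collection. Neither they nor any other section extends the promise to database lock, a final analysis plan or completion of the primary analysis.

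2. **When can the full primary model first be fitted?** The model for GAD-7 and PHQ-9 includes the Month 12 visit, which is the last in Table 1. For the whole sample it becomes possible only when the last Month 12 assessment is in, and that is when data collection is complete.

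3. **Do the two periods overlap?** The blind is guaranteed up to that event, and the full primary analysis can start only from it. The overlap that the text guarantees is nil. The overlap that the text permits is complete, because *until after* sets a minimum and the codes could stay in place.

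4. **Are data-dependent steps left on the far side of that event?** The section on data processing puts diagnostics and assumption checks before the key analyses and gives no rule for acting on them. The section on statistical approaches selects covariates by comparing the groups at baseline. Both depend on the data and neither is said to be done blind. The covariate rule does need the groups to be distinguished, but labels A and B are enough, so it does not itself require the key.

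5. **Does the sentence on unblinding procedures settle the matter?** No. The reason it gives is participant safety, so it concerns emergency unblinding during the trial, not the handling of the key at analysis.

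6. **Would coded arms hold if kept longer?** Not if the statistician also receives HAT, CRQ or STQ records. Only Digital PAI participants complete them, so their presence shows which code is which.

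**The case against.** The strongest reply is that the protocol never orders an early release. *Until after* is a floor, the statistician named is the one for the primary efficacy analyses, and all groups carry codes. A primary analysis on coded arms fits every word of the text. This stands. A reader might infer that the blind ends before the primary analysis begins and that the open choices will be made with the arms known. The documents state neither; they only fail to exclude it.

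A second reply is that rules for anomalies, the covariate list and similar detail belong in a statistical analysis plan, which may exist and is not shown. That also stands, and the absence of those lists is no part of this point. The point concerns a release event that the protocol does state, twice. A separate plan that kept the blind longer would go further than these two statements and should be matched by them.

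A third reply is that the blind as written already does useful work. It does: it covers the outcome assessors, and it covers the lead investigator while that person carries out periodic data quality checks (Data management). It would be wrong to say that the blind gives no protection.

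Finally, a reader might want to size the problem by simulating the best p-value over several specifications. That would not measure unblinding. If the test is two-sided (the protocol does not state sidedness), swapping A and B reverses the sign of the estimate and leaves the p-value unchanged. An analyst on coded arms could reach the same minimum. Such a figure reflects unfixed choices. The set of choices would also have to be assumed, and some candidates are ruled out by the text: a first slope ending at Month 12 would leave no second segment in a piecewise model.

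**Conclusion.** The point holds in limited form. The protocol guarantees the blind of the study analyst and the primary-efficacy statistician only to the end of data collection, which is when the full primary model first becomes possible. Nothing in the text stops data-dependent steps in that analysis from being taken with the arms known.

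The size is a gap in assurance, not a demonstrated bias, and no inflation of the error rate is claimed. The conclusion rests on two readings: that the full primary model is the one using all visits to Month 12, and that no unseen document binds the team to a longer blind. If an analysis plan already keeps the codes through the primary analysis, only the protocol wording needs to be brought into line. The change is worth making because it closes the gap at almost no cost and, with data collection still under way (Trial status), there is time to make it.

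**What to change.** Amend both statements under Study design so that the allocation key is released to the study analyst, the statistician and the lead investigator only when three conditions are met:

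1. the database is locked;
2. the analysis choices are final and in writing, including how anomalies are handled and how covariates are chosen;
3. the GAD-7 and PHQ-9 primary models have been run on arms labelled A and B.

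The second condition is needed alongside the third. Coding removes the ability to favour a direction, but it does not stop a choice among specifications by p-value.

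Add that HAT, CRQ and STQ data are held apart from the statistician until the key is released, since they would reveal the codes. Analyses that use them can follow afterwards.

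The cost is a change of wording, since the codes already exist, plus slight extra data handling: someone outside the primary analysis must prepare the coded file and keep the arm-specific measures separate.

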### Sample size and power

The *R* package *simr* [56] was used for power calculations, which simulated a multilevel model with time and group as fixed effects. The primary outcomes are anxiety and depressive symptoms, indexed by GAD-7 and PHQ-9 scores, respectively. Given the low-intensity nature of the Digital PAI and its evaluation against a Self-Monitoring Placebo as a placebo control [57], we expected the between-treatment effect sizes to range from small (Cohen’s *d* = 0.2) [26, 58] to moderate (*d* = 0.5) [24]. To achieve a statistical power of 81% while detecting small to moderate between-group efficacy effect sizes at a 5% significance level, a sample size of between 300 and 1,600 is required. Accounting for an estimated 50% attrition rate, our planned sample size was 1,200 (600 participants per group).

### Eligibility criteria and participant characteristics

Community-dwelling adults and tertiary students aged between 21 and 64 years old with self-reported scores between 5 and 14 on the GAD-7 (mild to moderate severity) and between 5 and 19 (mild to moderate-severe) on the PHQ-9 were eligible to participate in this RCT. They would need to be proficient in English, both in writing and orally, have a functional smartphone, and be based in Singapore in the next 15 months to ensure smooth protocol implementation. Low mania severity, as indexed by scores ≤ 6 on the Altman Self-Rated Mania (ASRM) scale [59], is another inclusion criterion. Exclusion criteria included participants who self-reported a score of 2 or 3 on item 9 of the PHQ-9 (“Thoughts that you would be better off dead, or of hurting yourself”), where such responses would prompt research personnel to engage in a suicide risk assessment and safety planning protocol. Participants who received a psychiatric diagnosis of bipolar disorder, psychosis, severe clinical anxiety, or depressive disorder from a mental health professional in the past 12 months are also excluded from the study.

### Study procedures

Prospective participants complete the brief screening survey to determine eligibility. Eligible and interested participants then attend the baseline visit, where they complete a 60-minute assessment battery comprising measures detailed below. The baseline Qualtrics-administered self-report battery assesses background information, academic and work functioning, learning history, mental health, personality, stressors, and related variables, as well as performance-based neurocognitive and social cognition tests. Learning history is defined as early life experiences, such as childhood trauma and family dynamics, that might contribute to present functioning. These pretreatment variables will be used to better understand modifiable predictors of symptom reduction and to develop treatment-matching rules [60, 61] that determine who benefits the most from the Digital PAI.

Study team members who are not involved in data analyses facilitate all baseline visits. After the baseline visit, participants will download an app and receive instructions three times daily (morning, afternoon, and evening) to engage with the Digital PAI or Self-Monitoring Placebo over a 6-week period from the baseline visit. Those assigned to the Digital PAI will receive a weekly 30-minute online lesson and thrice daily ecological momentary interventions (EMI) linked to the weekly intervention content, as detailed in subsequent sections. Conversely, those assigned to the Self-Monitoring Placebo will track their mood over the 6 weeks by completing a series of ecological momentary assessments (EMAs) without receiving any therapeutic content. The EMI and EMA protocols are fully automated using the mEMA Ilumivu platform, with time-contingent deliveries tailored to participants’ schedules. Participant engagement levels in both groups will be tracked through a log maintained in the backend. This platform automatically timestamps all responses and provides data security in HIPAA-compliant ways. More details on the Digital PAI, EMI, and EMA content, as well as study assessments, are provided below. Table 1 summarizes the schedule or time points at which these measures are administered.

**Table 1 Tab1:** Schematic summary of the time points of the administration schedule of specific measures

Timeframe	Initial study in-person visit		Six-week treatment		Long-term follow-up phases		
Measure	Screening	Baseline	Week 3	Week 6	Month 3	Month 6	Month 12
ASRM	X						
GAD-7	X		X	X	X	X	X
PHQ-9	X		X	X	X	X	X
ACS		X	X	X	X	X	X
ATQ		X	X	X	X	X	X
DARS		X	X	X	X	X	X
ERQ		X	X	X	X	X	X
MHC-SF		X	X	X	X	X	X
PANAS		X	X	X	X	X	X
PSQI		X	X	X	X	X	X
PSS		X	X	X	X	X	X
PVSS		X	X	X	X	X	X
SCS-SF		X	X	X	X	X	X
2BT		X					
BLERT		X					
Brief COPE		X					
CDS		X					
CTQ		X					
GADQ-IV		X					
GNG		X					
IRI		X					
PDSR		X					
Personality		X					
PHI		X					
PSAS		X					
RSES		X					
SCI		X					
SHPS		X					
Loneliness		X					
WCST		X					
CRQ				X			
STQ				X			
HAT			After each session				

‘X’ marks the time point of measurement administration

*2BT* 2-Back Task, *ACS* Attentional Control Scale, *ASRM* Altman Self-Rated Mania, *ATQ* Automatic Thoughts Questionnaire, *BLERT* Bell Lysaker Emotion Recognition Test, *Brief COPE* Brief Coping Orientation to Problems Experienced, *CDS* Cognitive Distortions Scale, *CRQ* Cultural Relevance Questionnaire, *CTQ* Childhood Trauma Questionnaire, *DARS* Dimensional Anhedonia Rating Scale, *ERQ* Emotion Regulation Questionnaire, *GAD-7* Generalized Anxiety Disorder-7, *GADQ-IV* Generalized Anxiety Disorder Questionnaire-Fourth Edition, *GNG* Go/No-Go, *HAT* Helpful and Hindering Aspects of Therapy, *IRI* Interpersonal Reactivity Index, *MHC-SF* Mental Health Continuum Short Form, *PANAS* Positive and Negative Affect Schedule, *PDSR* Panic Disorder Self-Report, *PHI* Pemberton Happiness Index, *PHQ-9* Patient Health Questionnaire-9, *PSAS* Pre-Sleep Arousal Scale, *PSQI* Pittsburgh Sleep Quality Index, *PSS* Perceived Stress Scale, *PVSS* Positive Valence Systems Scale, *RSES* Rosenberg Self-Esteem Scale, *SCS-SF* Self-Compassion Scale-Short Form, *SCI* Sleep Condition Indicator, *SHPS* Sleep Hygiene Practice Scale, *STQ* Satisfaction with Treatment Questionnaire, *WCST* Wisconsin Card Sorting Test

### Symptom assessments

Symptom severity will be assessed using a range of psychometrically reliable and valid self-report measures administered at various time points to evaluate both the proximal and distal differential efficacy of Digital PAI. The GAD-7 [49], PHQ-9 [62], and Dimensional Anhedonia Rating Scale (DARS) [63] are administered at screening or baseline, mid-treatment (Week 3), post-treatment (Week 6), as well as 3-, 6-, and 12-month follow-ups to monitor changes in anxiety, depressive, and anhedonia symptoms, respectively. The ASRM [59] is administered at the screening stage to assess possible exclusionary symptoms of mania. Furthermore, the symptoms of GAD and panic disorder are assessed using the GAD Questionnaire-Fourth Edition (GADQ-IV) [64] and the Panic Disorder Self-Report (PDSR) [65], respectively, at baseline, and these measures align with the Diagnostic and Statistical Manual, Fifth Edition (DSM-5) criteria [66]. This staggered yet holistic measurement method allows the assessment of both proximal symptom change and sustained maintenance of gains. Refer to Appendix B for more details on the psychometric properties of each assessment.

Additionally, participants may discontinue the Digital PAI or Self-Monitoring Placebo as they wish at any time. Study staff may stop participation if safety concerns arise, including the detection of suicidality at any follow-up assessment. In those scenarios, a suicide risk assessment and brief safety planning will be conducted for these participants.

### Process-based assessments

Most process-based assessments are administered at baseline to determine individual differences in psychosocial factors that may moderate or predict treatment response and distal outcomes. These assessments consist of the Childhood Trauma Questionnaire (CTQ) [67] to capture retrospective childhood maltreatment encounters; the Brief Coping Orientation to Problems Experienced (Brief COPE) [68] to measure coping strategies; the performance-based Bell Lysaker Emotion Recognition Test (BLERT) [69] to measure socioemotional processing; and the Emotion Regulation Questionnaire (ERQ) [70] to capture cognitive and behavioral ER habits. Further, baseline assessments measure global well-being with the Pemberton Happiness Index (PHI) [71]; perceived loneliness with the University of California, Los Angeles (UCLA) Loneliness measure [72]; subjective appraisal of stress with the Perceived Stress Scale (PSS) [73]; and personality traits with the Revised NEO Personality Inventory (NEO-PI-R) self-report [74]. In addition, at baseline, this RCT measures levels of PA and NA from the Positive and Negative Affect Schedule (PANAS) [75]; reward processing with the Positive Valence Systems Scale (PVSS) [76]; psychosocial well-being with the Mental Health Continuum Short Form (MHC-SF) [77]; trait self-compassion with the Self-Compassion Scale-Short Form (SCS-SF) [78, 79]; and self-esteem with the Rosenberg Self-Esteem Scale (RSES) [80]. Thinking errors are measured with the Cognitive Distortions Scale (CDS) [81] and Automatic Thoughts Questionnaire (ATQ) [82]. Trait empathy is assessed using the Interpersonal Reactivity Index (IRI) [83], a self-report measure. Most of these self-reports and 1 performance-based assessment (BLERT) will be collected only at baseline. However, a specific subset (ACS, ATQ, DARS, ERQ, GAD-7, MHC-SF, PANAS, PHQ-9, PSQI, PSS, PVSS, and SCS-SF) will be re-administered at mid-treatment, post-treatment, as well as 3-, 6-, and 12-month follow-ups to assess change across time (Table 1 and Appendix B).

